#### Effect factor analysis

2.9.2

If there are obvious differences between the groups in age, gender, disease type or condition before the test or there are factors that will significantly alter the curative effect, the analysts will need to consider these factors as covariates when comparing the groups. Covariance analysis or logistic regression analysis will be used, and the combination of drugs and other conditions will be listed in detail.

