**Methods/Design::**

A total of 333 participants will be randomly assigned to 2 acupoint treatment groups or 1 nonacupoint control group in a 1:1:1 ratio by a central stochastic system. The acupuncture groups are: the single acupoint group: Shenmen (HT7); and he compatibility acupoint group: Shenmen (HT7), Baihui (DU20), and Sanyinjiao (SP6). The observation period of this trial will be 10 weeks. All patients will be followed for 1 week before randomization (baseline phase). After randomization, the patients will receive 30 minutes of electro-acupuncture once per day for 5 weeks. In the fourth week after the treatment, follow-up will be performed once. The primary outcome will be the Pittsburgh sleep quality index score at 1 week before randomization and 2 and 8 weeks after randomization. The secondary outcomes will include data from sleep diaries, Athens insomnia scale scores, ShortForm-36 Health Survey scores, electroencephalogram technology results and polysomnogram) results. Patients will be required to complete a sleep diary every day during the treatment period. Patients will also undergo electroencephalogram technology and polysomnogram 1 week before randomization and 5 weeks after randomization. The other secondary outcomes will be measured 1 week before randomization and 5 and 9 weeks after randomization.

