### Sample size

2.8

A power analysis is calculated before conducting this trial, which α = 0.05 and power = 90%. According to the previous pilot study, percentages of responders for the primary endpoint are verum 87.5%, sham 25%. Therefore, the sample size in this trial can be estimated initially according to the following formula. Each group needs at least 111 patients (assuming a 20% dropout rate), 333 patients in 3 groups totally will be enrolled in the study.

$$n=\frac{2{\left(u_{\alpha }^{'}+u_{\beta }\right)}^{2}p(1-p)}{{\left(p_{1}-p_{2}\right)}^{2}}$$

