#### Validity analysis

2.9.1

The efficacy scores for week 0, week 2, and week 4 for patients with primary insomnia will be calculated using the difference between the treatment period and baseline period. These indicators will be described by mean, standard deviation, median, P5, P75, and maximum and minimum values. PP and ITT will be used to analyze the main indicators and overall indicators. Because this study is a multicenter randomized controlled clinical trial, the central effect on the therapeutic effect will be considered in the analysis.

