#### Safety analysis

2.9.3

Depending on the requirements of adverse reactions related to the control and treatment groups, adverse events and adverse reactions (the number of cases and the probability of occurrence) will be listed in a form, and the reasons for their occurrence will be described. If necessary, the *χ*^2^ test can be used for the statistical analysis of adverse reactions.

Statistical analysis will be performed using SAS9.1.3 statistical analysis software. *P* < .05 (α = 0.05) will be considered to be statistically significant.

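### Covariate adjustment of the efficacy comparison, including for baseline severity, depends on what the data show; one primary model with baseline PSQI and centre should be fixed in advance

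*Protocol article*

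**What the plan says.** Section 2.9.1 (Validity analysis) derives the efficacy scores "using the difference between the treatment period and baseline period" and lists descriptive statistics for them. It names no test for comparing the arms. On centre it says only that "the central effect on the therapeutic effect will be considered in the analysis".

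Section 2.9.2 (Effect factor analysis) sets the rule for covariates. They come in under either of two conditions:

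- "If there are obvious differences between the groups in age, gender, disease type or condition before the test";
- where there are factors that materially change the treatment effect.

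The last item in the first condition is most naturally read as baseline severity. The section then allows either analysis of covariance or logistic regression and does not say when each applies.

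Section 2.7.1 (Outcome measurement) makes PSQI the primary outcome and has every patient complete it one week before randomization. No section names baseline PSQI as a covariate to be used regardless of balance.

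**The concern.** Patients are allocated centrally and at random to "2 acupoint treatment groups or 1 nonacupoint control group in a 1:1:1 ratio", so any baseline difference between arms is due to chance. How large it looks is a poor guide to which covariates belong in the model. Prognostic strength is the better guide, and it can be named beforehand; baseline PSQI is the obvious candidate.

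Two things are at stake.

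- **Error control.** With no threshold on either trigger and two model types on offer, an analyst can see more than one result before deciding which is primary.
- **Precision.** A change score uses baseline PSQI with its slope fixed at 1. ANCOVA estimates the slope and is at least as precise, apart from a negligible loss of degrees of freedom.

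This is more than detail left to an analysis plan. The article states the rule, so a plan that followed it would inherit the problem and a plan that did not would contradict it.

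**Working it through.** **Inputs.** The article gives no SD, no baseline-to-follow-up correlation (r) and no PSQI difference, so there is no figure on this point to reproduce. From Section 2.8 (Sample size) only the group size is needed: "Each group needs at least 111 patients (assuming a 20% dropout rate"), and 111 × 0.8 = 88.8, so about 89 evaluable per arm. The nominal level is 5% (Section 2.9.3: "α = 0.05) will be considered to be statistically significant").

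As an aside, 111 does not follow from the stated rates ("percentages of responders for the primary endpoint are verum 87.5%, sham 25"%). With p = (0.875 + 0.25)/2 = 0.5625, two-sided α of 0.05 and 90% power, the printed formula gives 2 × (1.960 + 1.282)² × 0.5625 × 0.4375 / 0.625² = 13.2, so 14 per group, and 14/0.8 = 17.5, so 18 with dropout. That is a separate matter and nothing below rests on it.

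**Step 1: choice of model under the null.** 20,000 simulated two-arm trials, 89 per arm, no treatment effect, normal scores, equal SDs at both times, assumed r. Monte Carlo standard error is about 0.2 percentage points, except in the last row, which uses only the imbalanced trials.

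| Type I error | r = 0.3 | r = 0.5 | r = 0.7 |
|---|---|---|---|
| Change score always | 4.8% | 5.0% | 4.8% |
| ANCOVA always | 4.8% | 5.1% | 4.8% |
| Better of the two, chosen freely | 7.5% | 7.5% | 6.6% |
| ANCOVA only if baseline differs at P<0.05, else change | 3.8% | 4.4% | 4.4% |
| Change score, in trials where baseline differs at P<0.05 | 25% | 18% | 13% |

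Either model fixed in advance holds its level. Inflation comes from discretion. The mechanical rule errs on the conservative side because it replaces the change score in the trials where the change score misleads.

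**Step 2: precision.** Take the follow-up variance as 1 and let k = baseline SD / follow-up SD.

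- Change-score variance: 1 + k² − 2kr
- ANCOVA variance: 1 − r²
- Ratio, ANCOVA to change score: (1 − r²)/(1 + k² − 2kr)
- Change-score variance minus ANCOVA variance: k² − 2kr + r² = (k − r)², which is never negative

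| | r = 0.3 | r = 0.5 | r = 0.7 |
|---|---|---|---|
| k = 1 | 0.91/1.40 = 0.65 | 0.75/1.00 = 0.75 | 0.51/0.60 = 0.85 |
| k = 0.7 | 0.91/1.07 = 0.85 | 0.75/0.79 = 0.95 | 0.51/0.51 = 1.00 |

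Taking 1 minus the square root of each ratio, the standard error falls by 19%, 13% and 8% at k = 1, and by about 8%, 3% and 0% at k = 0.7. A k below 1 is plausible because Section 2.2.2 requires PSQI above 7 at entry, which can narrow the baseline SD.

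**The case against.** The strongest reply is that the text is milder than it looks. Section 2.9.1 names no test, so defining a difference does not commit the trial to an unadjusted comparison. Section 2.9.2 does name analysis of covariance, and ANCOVA of change with baseline as covariate gives the same treatment effect as ANCOVA of the follow-up score. The second trigger could mean factors already known to be prognostic. No baseline significance test is prescribed, and covariate lists and the form of the centre term are often left to an analysis plan. All of this is fair, and the brief wording on centre is no defect in itself. What stands is that adjustment for baseline condition is stated to depend on visible imbalance, with no threshold and no single model.

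Four stronger readings are tempting, and the article does not support them.

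- **ANCOVA is worth 18–54% more patients.** That range (1/0.85 to 1/0.65) needs equal SDs and r of 0.3 to 0.7. At k = 0.7 the gain is about 18%, 5% and 0%.
- **Change scores are biased by regression to the mean.** Over randomizations the change-score contrast is unbiased. The trouble is conditional on chance imbalance, which is the case in which Section 2.9.2 calls for adjustment.
- **The stated rule inflates type I error.** Applied mechanically at P<0.05 it does not; free choice does.
- **The compatibility versus single-acupoint comparison is short of power.** Section 2.8 gives only a verum and a sham rate and no difference between the two active arms, so the article does not show this.

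**Conclusion.** The point holds in this form: the protocol article makes covariate adjustment, including for baseline severity, depend on observed data without a threshold, leaves two models open, and does not fix baseline PSQI as a covariate.

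Its size is moderate. Discretion between the two models can take a 5% test to about 6.6–7.5%. That rests on assumed r of 0.3 to 0.7, equal SDs and one two-arm comparison. Where r is close to k, the ANCOVA slope r/k is close to 1, the two analyses nearly coincide, and the inflation shrinks. The gain in precision runs from none to a 35% reduction in variance over the assumptions shown, and the article gives no basis for choosing within that range. ANCOVA is never materially worse.

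The variance ratios apply to a PSQI score. They do not carry over if the primary endpoint is responder status, on which Section 2.8 bases the sample size.

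**What to change.** 1. First reconcile the primary timepoint and endpoint type. The Abstract puts PSQI at weeks 2 and 8 after randomization, Section 2.7.1 at weeks 5 and 8, and Section 2.9.1 scores efficacy at weeks 0, 2 and 4. Section 2.8 sizes the trial on responders, while Section 2.9.1 analyses score differences.
2. Name one primary model: ANCOVA, or a mixed model, of PSQI on arm, baseline PSQI and centre (six hospitals), applied whatever the observed balance. If the primary endpoint is responder status, use logistic regression with the same covariates.
3. Delete both data-driven triggers from Section 2.9.2.
4. Keep age, sex and acupuncture expectation, all already recorded under Section 2.7.1, in one named sensitivity model.

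The cost is a change of wording, made before outcomes are compared by arm. It needs no new data, and the model spends one degree of freedom on baseline PSQI and five on centre. Step 1 is the only part that calls for a real decision.

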#### Safety analysis

2.9.3

Depending on the requirements of adverse reactions related to the control and treatment groups, adverse events and adverse reactions (the number of cases and the probability of occurrence) will be listed in a form, and the reasons for their occurrence will be described. If necessary, the *χ*^2^ test can be used for the statistical analysis of adverse reactions.

Statistical analysis will be performed using SAS9.1.3 statistical analysis software. *P* < .05 (α = 0.05) will be considered to be statistically significant.

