## Introduction

1

Insomnia is characterized by dissatisfaction with sleep quantity or quality and is associated with difficulty falling asleep and maintaining sleep.^[1]^ Most reports suggest that the prevalence rates of insomnia are 5% to 15%.^[2–5]^ Insomnia is a chronic problemand has been associated with erectile dysfunction,^[6]^ burning mouth syndrome,^[7]^ depression, ^[8]^anxiety,^[9]^ and functional gastrointestinal disorders.^[10]^ There are many ways to treat or relieve insomnia, including the “guided fantasy” technique,^[11]^ operation of a homeostatic sleep switch,^[12]^ and cognitive behavioral treatments.^[13]^ Among the dominant disciplines in traditional Chinese medicine, acupuncture and moxibustion are widely applied and promoted in clinical practice due to their safety and efficacy. Many Chinese and foreign studies have demonstrated that acupuncture has hypnotic effects and is effective in treating insomnia.^[14]^ However, questions related to the selection of acupoints to treat insomnia, as well as whether single acupoints or compatibility acupoints have better therapeutic effects, have affected clinical acupoint treatment, and these questions remain open.

Therefore, we will perform this multicenter, randomized, controlled, large-scale trial, first aiming to investigate whether acupuncture is effective in treating insomnia through a comparison with a non-acupoint control group. Second, we will compare the clinical efficacy of single acupoints with that of compatibility acupoints in the treatment of primary insomnia. The work reported in this article is financed by the National Basic Research Program (973 Program: 2014CB543100) in China and is registered with an identifier (NCT02448602) by Clinical Trials.gov in the United States of America.

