### Design

2.1

This study will be a multicenter, large-sample, randomized, controlled trial conducted in the following 6 hospitals: Affiliated Hospital of Changchun University of Traditional Chinese Medicine; The First Affiliated Hospital of Hunan University of Traditional Chinese Medicine; Hengyang Affiliated Hospital of Traditional Chinese Medicine; People's Affiliated Hospital of Traditional Chinese Medicine; China-Japan Friendship Hospital of Jilin University; and QiLu Hospital of Shandong University. The design of this study is in accordance with the guidelines of the HIS Committee on Clinical Trials in Migraine.^[15]^

This trial will include 3 groups (Fig. 1, Fig. 2 ): 2 acupoint treatment groups (single acupoint and compatibility acupoint groups) and 1 nonacupoint control group. A central stochastic system will be used to distribute the patients among the 3 groups equally.

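### Three arms and two aims share one flat P < .05 rule with no stated overall test or order; if all three arms are equal, the chance of a false claim is up to about 12%

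*Protocol article*

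**What the plan says.** The Design section sets up "2 acupoint treatment groups (single acupoint and compatibility acupoint groups) and 1 nonacupoint control group", and the abstract allocates patients "in a 1:1:1 ratio by a central stochastic system". The Introduction gives two aims. One is "first aiming to investigate whether acupuncture is effective in treating insomnia through a comparison with a non-acupoint control group". The other reads: "Second, we will compare the clinical efficacy of single acupoints with that of compatibility acupoints in the treatment of primary insomnia".

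The decision rule stands at the end of section 2.9.3 (Safety analysis), straight after the software sentence. It gives the threshold P < .05 and continues "α = 0.05) will be considered to be statistically significant". By its position and wording it reads as the rule for all analyses, not only safety. Section 2.8 (Sample size) also works with an unadjusted level, "which α = 0.05 and power = 90" percent, for a single verum against sham contrast.

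Two further features bear on the number of tests:

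- **Times.** The primary outcome, the PSQI, has two assessments after randomization: weeks 2 and 8 in the abstract, weeks 5 and 8 in section 2.7.1.
- **Populations.** Section 2.9.1 says "PP and ITT will be used to analyze the main indicators and overall indicators" and names neither as primary.

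Section 2.9.2 mentions covariance analysis or logistic regression for comparing groups. The article states no overall three-arm test, testing order or multiplicity adjustment.

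**The concern.** Both aims are headline aims; the article's Discussion paragraph in the abstract even presents the second as what the trial will establish. Answering both takes more than one comparison between arms. If each comparison is read against the same 0.05, the 5% error rate applies to each test and not to the set of main claims. Two PSQI times and two populations, with no primary named, leave further room to choose the favourable result. At stake is whether a positive report on any one of these comparisons carries the stated 5% error rate.

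**Working it through.** **Inputs.** From the article: three equal arms, level 0.05 per test (taken as two-sided, since the article does not say), 111 per arm and 20% dropout, so 111 × 0.8 = 88.8, or 88 evaluable per arm. Assumed: the correlation between the two PSQI times, which the article does not give.

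**1. The plan's own figure.** The section 2.8 formula with p = (0.875 + 0.25)/2 = 0.5625 gives n = 2 × (1.960 + 1.282)² × 0.5625 × 0.4375 / 0.625² = 13.2. That is 14 per group, or 14/0.8 = 17.5, so 18 with dropout. The stated 111 is not reproduced. Repeating the calculation at 0.05/3, two-sided, gives 17.0, so 18 per group and 23 with dropout. So a hidden adjustment of alpha does not explain 111 either. That mismatch is a separate matter and does not affect the figures below.

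**2. Chance of at least one false claim, all three arms equal, one time, one population.**

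| Reading of the aims | Calculation | Result |
|---|---|---|
| Three pairwise tests | studentized range, P(q > 1.96 × √2), 3 groups | 12.2% |
| Each acupuncture arm against control only | two normal statistics with correlation 0.5 (shared arm) | 9.1% |
| Pooled acupuncture against control, and single against compatibility | orthogonal contrasts, 1 − 0.95² | 9.75% |

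Simulation with 88 per arm (400,000 runs) gives 12.1% for the first row. With binary responders it is 12.7% to 13.2%, the excess coming from discreteness.

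**3. When one arm truly differs.** With three arms, any two pairwise equalities imply the third. So unless all three arms are equal, at most one pairwise null can be true, and it is tested at 5%. In the article's planning scenario (87.5% in both acupuncture arms, 25% in control) the only possible false claim is single against compatibility; its simulated rate is 4.9%.

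**4. Two PSQI times.** Six tests with all arms equal give 21.3% at correlation 0.5 and 19.6% at 0.7. With one true pairwise null remaining, testing it at both times with correlation 0.5 gives 9.1% (the same bivariate calculation as the second row above).

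**5. Overall three-arm test first, then pairs at 0.05.** One time, one population:

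- All arms equal: 5.0%.
- Two arms equal and the third shifted by 0.2 to 2 SD: 3.8% to 5.0% on the equal pair, and up to 5.4% with binary data because of discreteness.
- The same procedure run separately at two times: 8.4% to 9.6% for correlations 0.7 to 0.3. The overall test is therefore not enough unless one time is named as primary.

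**The case against.** The strongest case on the other side has four parts.

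- **Nothing wrong is stated.** The article nowhere says that three pairwise tests will be run unadjusted. A flat 0.05 is even compatible with the procedure recommended here, which uses 0.05 at every step, and an unseen SAP may contain it. This stands as a limit: unadjusted pairwise testing is inferred from the general rule. But the article does publish a rule, and as written that rule does not say which claims share the 5%. The narrower readings without an order also exceed it.
- **The aims are already ordered.** They are numbered first and second. However, nothing makes the second test conditional on a positive first one. If a fixed sequence was meant, saying so would largely settle the point, although the first aim would still need to be defined as one pooled contrast or as two comparisons.
- **Separate questions need no joint control.** This is partly a matter of preference, and it supports treating the point as an inexpensive improvement and not a fatal flaw.
- **The 12% is a worst case.** This stands in full. It requires all three arms to be equal, which is far from the planning assumption.

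**Conclusion.** The point holds in a limited form. One flat P < .05 rule, with no overall test, order or adjustment, allows about 12% family-wise error if the three pairwise tests are each taken at 0.05 and all arms are equal, or 9% to 10% with two contrasts. For one time and one population the error is otherwise at most about 5%.

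Three stronger readings are not supported:

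- A reader might infer that the trial's actual error rate is 12%. That holds only when no arm differs from any other.
- A reader might infer a rate of 20% or more. That rests on correlations which the article does not supply, and on treating both PSQI times as alternative routes to success, which it does not state.
- A reader might infer that the trial may declare success on any single significant test. No success rule is written at all; the gap is that none is fixed.

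Confidence is moderate, because the SAP is not shown.

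**What to change.** Add a few sentences to section 2.9 before unblinding:

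1. Name one PSQI assessment after randomization as the primary time, once the weeks in the abstract and in section 2.7.1 have been reconciled, and name ITT as the primary population.
2. Test the three-arm comparison first at two-sided 0.05 (the two-degree-of-freedom group effect in the chosen model).
3. Only if that is significant, test the three pairwise comparisons, each at two-sided 0.05.
4. Treat the other time, PP and the secondary outcomes as supportive.

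With exactly three arms, steps 2 and 3 form a closed procedure, so no alpha has to be split. The same step would not be enough with four or more arms.

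The cost is wording, plus one small loss: a pairwise P just below 0.05 does not count if the overall test fails. At the planned 87.5% against 25%, the overall test passes in essentially every trial. In an illustrative less favourable case (single acupoint equal to control, compatibility 0.49 SD better, 88 per arm; assumed values), power for compatibility against single falls from 90.1% to 87.8%.

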## Discussion

3

This trial is a portion of the National Basic Research Project (973 Program, 2014CB543100). The 973 Program, the national key basic research development plan, aims to solve major scientific problems associated with national strategic needs and advance the frontiers of science that will play an important role in understanding the world.

Because acupuncture works quickly and is easy to perform, it has greater application and popularization value clinically. Acupuncture was listed in the “representative list of intangible cultural heritage of humanity” and is widely used in >160 countries and regions in the world. The normative selection of acupoints in clinical practice is a major scientific problem, as is determining the development of acupuncture theory and the improvement of clinical efficacy. It is also the historical mission of modern acupuncture practitioners.

The patterns of acupoint compatibility are many and varied in clinical practice. The basic pattern is compatibility according to the location and meridian; however, each acupoint has a specific therapeutic effect, and only the appropriate compatibility will achieve the best effect. Therefore, identification of scientific and reasonable acupoint compatibility is the key to improving the effectiveness of acupuncture.

Generations of physicians have agreed that acupoint compatibility can enhance the curative effect, and many propose the compatibility method. Some achievements have been made in the study of the compatibility of modern methods. There are 874 related studies and reviews worldwide. However, there is no scientific basis regarding whether the compatibility acupoints are superior to a single acupoint, and there is a lack of evaluation systems of the variable effect between various acupoints and the optimal compatibility formula. The key factors that influence the effect of compatibility are also not clarified. Therefore, the main goals of compatibility acupoint research are definition of the optimal formula of compatibility, evaluation of the methodology, and explanation of the influencing factors of the various effects of compatibility.

For this trial, we chose insomnia as an outcome measure, guided by traditional Chinese medicine and acupuncture, combined with acupuncture clinical research standards, clinical epidemiology, and evidence-based medicine. We adopted a multicenter, maximal sample randomized controlled trial approach. By means of objective and scientific evaluation, we will compare the various effects of compatibility acupoints.
